## Abstract

**Background:**

National birth rates among adolescents have consistently decreased since 1991, yet substantial disparities remain, particularly among youth in foster care, who experience higher risks of unintended pregnancies and sexually transmitted infections. Few sexual health programs rarely address the specific needs of foster youth or incorporate youth perspectives into their design, development, and implementation.

**Objective:**

This study aims to refine, pilot-test, and evaluate Next4You, a fully mobile, youth-centered sexual health education platform tailored specifically for adolescents in or transitioning from foster care. The program intends to reduce sexual risk behaviors and related psychosocial outcomes by promoting healthy relationships, sexual wellness, contraception use, communication skills, self-respect, and wellness education.

**Methods:**

Next4You is a fully mobile, self-paced, 4-week intervention evaluated using an individual-level randomized controlled trial involving a target sample of 500 youths aged 16‐19 years with current or previous foster care experience in California. Participants are randomly assigned to either the intervention group, which receives access to Next4You modules, or the comparison group, which accesses general health materials through a similar web platform. Both groups complete baseline, 3-month, and 9-month follow-up surveys. Immediately following the 9-month follow-up survey, participants in each group receive access to the platform they were not initially assigned. Data collection assesses contraceptive behaviors, sexual communication, consent self-efficacy, and knowledge related to health rights and financial literacy. Intervention engagement is tracked through platform analytics, and qualitative interviews supplement data collection. Data analysis will adhere to intent-to-treat principles, using multilevel regression models to assess impacts.

**Results:**

Funding was awarded in 2021, with institutional review board approval in October 2022. Intervention development lasted approximately 7 months, engaging foster youth in a co-design process to ensure relevance and cultural competence. Study recruitment began in September 2023, continuing until May 2025. Final data collection is anticipated by March 2026, followed by data analysis.

**Conclusions:**

Next4You presents an innovative approach to sexual health education by addressing critical gaps in sexual health education for foster youth through mobile technology. If effective, Next4You could provide another evidence-based option for promoting sexual health among foster youth, guiding policymakers and practitioners in adopting similar trauma-informed and youth-centered interventions.

## Introduction

### Background and Rationale

National birth rates for adolescent women have continuously declined since 1991, falling to 5.6 per 1000 for 15‐ to 17-year-olds (approximately an 85% decrease) and to 25.8 per 1000 for 18‐ to 19-year-olds (approximately a 73% decrease) by 2022 [1]. This improvement has been attributed to a variety of factors, including increased use of contraception facilitated by improved access to clinical services, publicly funded adolescent pregnancy prevention programs, and comprehensive sexual health education [2,3]. Despite this progress, substantial disparities in birth rates persist by race, ethnicity, socioeconomic status, geographic location, and some populations [1]. In particular, foster youth are at a higher risk for unplanned pregnancy and sexual risk behaviors that lead to sexually transmitted infections (STIs). One in three young women in foster care becomes pregnant at least once by age 17‐18 years, with more than half experiencing a pregnancy by age 19 years, twice the rate of their peers not in foster care [4-6]. Young men in foster care are also at high risk for getting someone pregnant by age 19 years [4]. Youth in foster care are more likely than their peers to have had sexual intercourse, to have engaged in transactional sex, and to not have used birth control at last sex [6]. While 70% of pregnant young women in foster care did not plan their pregnancy, only a quarter of them were using birth control when they became pregnant [6], demonstrating a clear gap in prevention services reaching vulnerable youth [7-9]. Youth in foster care may be using birth control inconsistently or incorrectly because they experience instability in access to sexual health information and services, such as changes in caseworkers and living arrangements, and a lack of coordination among agencies providing care [4,5,10]. Additionally, many vulnerable youth have concerns about provider attitudes, privacy, and stigma when they access services [8]. LGBTQ youth, who are disproportionately represented in foster care and have an increased risk for pregnancy and STIs, face additional challenges in accessing health services and education that are inclusive and represent LGBTQ youth’s experiences, relationships, and identities [8,11,12].

For youth in foster care, there are few sex education programs designed specifically for them, and none that are evidence-based and available through the teen pregnancy prevention evidence review use a fully technology-based approach [13]. *Power Through Choices* was the first sex education program designed exclusively for foster youth to be evaluated by a randomized controlled trial [14]. This 10-session program used interactive methods to support youth in developing critical knowledge and sexual decision-making skills. Youth participating in the program were less likely to engage in sexual intercourse without birth control in the past 3 months at 6-month follow-up and had significantly lower odds of ever being or getting someone pregnant at 12-month follow-up than control youth. This program demonstrates that sexual health education can be implemented effectively with foster youth in nonclassroom settings. However, similar to other traditional sexual health education programs, there are limitations to a lengthy, multisession program among a population where high instability is associated with increased risk of pregnancy [5]. And when vulnerable youth cannot access information from trusted sources such as educators and providers, they may turn to the internet [12]. In a nationally representative survey, more than 80% of adolescents reported that they have sought health advice on the internet, with 34% modifying their behavior based on what they found [15]. Mobile technology is almost universally accessible—95% of adolescents have access to a smartphone regardless of gender, race and ethnicity, and socioeconomic status, and the majority (89%) are accessing the internet at least several times a day [16]. Yet, to our knowledge, there has been only one fully mobile sexual health intervention for young people that has been rigorously evaluated, and none that have been designed and evaluated specifically for youth in foster care [13,17].

Engaging youth in the design of interventions that impact their health and well-being is believed to support young people’s development [18], strengthen programs and services [19], and lead to social, political, and economic benefits [20]. Engagement in these processes is also what young people want [19]. Yet, sexual health interventions are rarely designed in collaboration with young people, especially those from systemically impacted communities such as youth in foster care [21]. Additionally, many existing sexual health interventions that meaningfully involve youth lack rigorous evidence on their ability to engage youth and impact health outcomes [21].

Young people, including those in foster care, routinely identify relationships and relationship health as important areas of focus [22]. Romantic relationships play a significant role in adolescent development [23]. By middle adolescence, most young people have been involved in at least one romantic relationship [24], a context in which most sexual interactions occur [25]. Adolescence is a period where young people begin to develop standards and expectations for relationships and build their communication skills. For youth in foster care, these tasks may be more difficult if they have experienced contexts where neglect, aggression, and violence are modeled [26]. Thus, youth in foster care are at increased risk for experiencing intimate partner violence and, because of prior trauma, may be more vulnerable to negative health impacts from intimate partner violence [27]. Yet, developmental psychologists emphasize that relationships developed during adolescence represent a new period where past models of relationships may be reshaped [23], an incredible potential to change unhealthy models and carry positive ones into adulthood, underscoring the potential impact of this content on adolescents’ well-being.

### Study Objectives and Research Questions

The primary study objectives are as follows: (1) refine and update the Next4You mobile responsive platform using trauma-informed and healing-centered principles, centering the voices of youth in foster care and engaging them directly in development; (2) pilot test the updated intervention and planned evaluation activities with youth representing the priority population and finalize based on pilot data and insights from youth and program partners; (3) assess the effectiveness of the new intervention using a randomized controlled trial; (4) develop an intervention manual and implementation package (eg, logic model, core components, adaptation guidelines, and fidelity tool) to support replications; and (5) collect other implementation data and document lessons learned throughout the study.

Textbox 1 summarizes the primary and secondary research questions for the study.

Textbox 1.Primary and Secondary Research Questions
**Primary research question**

*Three months following the intervention:*
1. What is the effect of the 4-week Next4You intervention on the prevalence of choosing abstinence or using condoms among participants who had vaginal or anal sex in the past 3 months?
**Secondary research questions**

*Nine months following the intervention:*
1. What is the effect of the 4-week Next4You intervention on the prevalence of choosing abstinence or using condoms among youth in foster care who had vaginal or anal sex in the past 3 months?
*Three and nine months following the intervention period:*
2. What is the effect of the 4-week Next4You intervention on rates of condomless vaginal or anal sex?3. What is the effect of the 4-week Next4You intervention on sexual consent self-efficacy?4. What is the effect of the 4-week Next4You intervention on sexual communication self-efficacy?5. What is the effect of the 4-week Next4You intervention on condom use attitudes?6. What is the effect of the 4-week Next4You intervention on contraceptive use attitudes and beliefs?7. What is the effect of the 4-week Next4You intervention on experiences with equity and power balance in relationships?8. What is the effect of the 4-week Next4You intervention on knowledge of health care rights and location of services?9. What is the effect of the 4-week Next4You intervention on contraceptive use (specifically experience with condom errors)?10. What is the effect of the 4-week Next4You intervention on knowledge of educational rights and programs?11. What is the effect of the 4-week Next4You intervention on financial literacy knowledge?

## Methods

### Study Design Overview

Next4You will be tested using an individual-level (randomized controlled trial) involving up to 500 young people ages 16‐19 years with former or current experience in the California foster care system. Half will be assigned to an intervention group and the other half to a comparison group. The study survey will be collected at three time points: baseline (ie, after assent and consent and before randomization) and 3 and 9 months after a 4-week intervention period (applied to both the intervention and comparison groups). The evaluation of Next4You was designed to meet the Institute of Education Sciences’ *What Works Clearinghouse* (WWC) design standards without reservations [28]. Figure 1 presents the CONSORT (Consolidated Standards of Reporting Trials) flow diagram illustrating participant enrollment, allocation, follow-up, and analysis for the study.

**Figure 1. F1:**
[figure not shown]
CONSORT (Consolidated Standards of Reporting Trials) diagram for the Next4You study.

#### Study Setting

The study will be completed digitally, among participants who have been referred to the study through partner organizations in 24 counties throughout California.

#### Eligibility Criteria

Youth must meet the following criteria to be eligible for the study: (1) age 16 to 19 years at time of study enrollment; (2) currently in foster care or formerly in foster care (and were in foster care on or after their 13th birthday); (3) currently residing in California; (4) proficient in English; and (5) have access to a tablet, laptop, desktop computer, or phone that is Wi-Fi- or cellular-enabled.

They also had to be free of severe mental health issues and have the cognitive ability to meaningfully engage with the web platform as determined by the recruitment ambassadors.

### Intervention and Comparison Protocols

#### Intervention Condition

Participants randomized to the active intervention condition will receive access to Next4You, a fully mobile intervention designed to reduce rates of unintended pregnancy and STIs among young people currently or recently in the California foster care system. The platform was designed in partnership with foster care youth and with input from community-based organizations serving this population. The responsive, web-based platform can be accessed by young people at any time from an internet-enabled mobile device.

The intervention features 6 content modules (Table 1): Sexual Wellness, Contraception, Relationships, Respecting Self and Partners, Communication, and Building Wealth and Wellness (eg, financial literacy, educational rights, and mental health), with a total instructional time of approximately 3 to 4 hours. Each module includes 5‐12 microlessons, designed as brief, informal snippets of content that are 5 minutes or less; focused on a single learning concept; and are delivered through diverse approaches such as games, videos, quizzes, and others [29]. One advantage of this method includes the repeatability of the content in time, place, and format preferred by most young people [30]. In addition to microlearning, the site includes gamification features, a youth-designed retention strategy to increase motivation to engage youth in the content.

**Table 1. T1:** Intervention modules.

Module	Microlessons, n	Brief description of module content
Sexual Wellness	9	Defining sexual wellness; sexual identity and orientation; sexually transmitted infections and ways to reduce risk; using and accessing health care to maintain sexual wellness; sexual boundaries; sexual and reproductive health rights; sexual anatomy and tips for increasing pleasure.
Relationships	10	Elements of a safe and secure relationship; factors that suggest it may be time to end a relationship; tips on navigating a breakup; navigating loss and feelings of rejection after a relationship ends; intimate partner violence; love bombing; strengthening and building connection in relationships; exploring factors that make young people with lived experience in foster care more susceptible to trafficking; exploring power and control behaviors that may show up in relationships.
Communication	7	“I” versus “you” statements; preparing for having difficult conversations; strategies for managing emotions that may surface during difficult conversations; strategies for de-escalating conversations; strategies for active listening to improve communication skills.
Respecting Self and Partners	7	Self-love and self-worth; affirmative consent; what respecting a partner includes; personal boundaries; strategies for navigating different personal boundaries; gender and gender identity.
Contraception	5	Condom use and steps; common methods of birth control; withdrawal from a harm reduction perspective; contraception rights; options if methods of contraception fail.
Building Wealth and Wellness	12	Passion and purpose; educational rights; college transition and support services; financial rights; coping skills; financial aid options; trauma—building resilience and navigating past trauma; mental health; budgeting; body image.

The Next4You platform includes a total of 50 microlessons, and participants earn points for each completed lesson. To motivate early engagement with the website, participants receive a US $25 e-gift card upon completing 5 lessons. Subsequent points are banked, and the remaining incentive amount is distributed at the end of the 4 weeks, based on the total amount of points earned. Participants may earn up to US $100 in e-gift cards for completing all 50 microlessons. In addition to lesson completion, participants can earn up to US $25 in bonus incentives through all 4 achievement badges: Start Up, On Fire, My Faves, and Consistency. In total, participants may earn a maximum of US $125 in e-gift cards over the 4-week program period.

The online platform will collect paradata in the form of timestamps and counts of user sessions for all actions performed by each user, thereby allowing for calculation of the time spent engaging with the intervention (including total time spent on each microlesson, modules, and engaging with various activities and resources), frequency of logins, and the amount of completed content. Users will be automatically logged out after approximately 10 minutes of inactivity to protect privacy and reduce the likelihood of inflated duration data. The evaluation will use the duration data to conduct exploratory analyses examining differing levels of exposure and the relation to study outcomes.

#### Intervention Conceptual and Development Frameworks

The development of the Next4You intervention draws upon other pertinent knowledge bases to center youth voice through a youth participatory process and draws on the latest research in positive youth development and microlearning to strengthen the intervention’s content and strategies (see the screenshots in Multimedia Appendix 1). Positive youth development is a strength-based approach used to promote adolescents’ prosocial competencies and build skills related to their positive health and well-being [31]. The adolescent development literature guided Next4You’s relationship development content and helped ensure it is age appropriate [23]. The intervention also draws on dual process theories to address the social-emotional and cognitive influences on sexual decision-making [32]. Finally, the intervention draws from social cognitive theory both in terms of key constructs in skill acquisition, such as building self-efficacy or confidence in one’s ability to perform a skill, and in shaping the process of learning, such as through using observational learning or modeling during instruction [33].

#### Intervention Co-Design Process

Engaging youth with lived experience in the foster care system as subject matter experts was an essential first step in developing the Next4You platform and its content. This approach provided a unique opportunity to deliver accurate, inclusive, culturally competent, and on-demand information, resources, and tools tailored to the needs of transition-age youth. To refine and enhance the platform before piloting, the team used youth participatory methods to engage these subject matter experts. These methods incorporate positive youth development principles, emphasizing the importance of engaging young people as partners by respecting their knowledge, insights, expertise, and leadership [34]. Recognizing that youth in foster care often experience trauma, we used trauma-informed and healing-centered principles when engaging co-designers, including safety, equity, empowerment, and resilience. This ensured that the co-design process was inclusive, culturally relevant, and supportive, even when difficult topics arose.

The co-design process involved 9 participants, ages 19‐22 years, from California, who engaged individually and as part of a group over 7 weeks through weekly 90-minute meetings. The facilitation approach was intentionally structured yet flexible. The sequence included 2 sessions on discovery (eg, community building), 2 on defining (research and product design and function), and 3 on designing content for intervention modules, concluding with a design and testing session. Slide decks structured each meeting, but sessions were highly interactive, incorporating icebreakers, small-group discussions, and digital tools (eg, Mentimeter or Kahoot). Participants were invited to be active cocreators rather than passive reviewers; facilitators used semistructured prompts such as “What keeps users coming back?” or “What does wellness mean to you?” to elicit ideas that shaped both content and user experience. Through this process, participants influenced the platform’s esthetics, navigation, and functionality, including customizable color schemes, authentic imagery, gamified features, and microlesson delivery. They identified priority content areas and co-developed stories, scenarios, and audio narration reflecting real experiences. The team used mockups and mood boards to align design decisions with participant input and maintained engagement between sessions through asynchronous channels (eg, GroupMe). Following co-design, pilot testing of 18 lessons yielded highly positive feedback. Participants recommended adding more interactive activities, videos, and visual animations, as well as expanding life-skills content such as improving communication with adults in positions of authority including teachers and supervisors. These refinements strengthened both usability and relevance for youth transitioning from foster care.

By centering youth as co-designers, the Next4You project produced a platform that authentically reflects their experiences and priorities, demonstrating the power of participatory design to advance youth-driven innovation in adolescent health.

#### Comparison Intervention

Youth randomized to the comparison condition will have access to a mobile-responsive website featuring digital resources focused on nutrition, sleep, stress and anxiety, and exercise. Consistent with the intervention group, participants in the comparison group will have unlimited access to the general health digital resources for the initial 4-week period. Throughout the evaluation, youth assigned to the control condition will also continue to receive the standard resources and services typically available to them through their involvement in the foster care system. The comparison condition was selected to establish an effective treatment contrast [35] by isolating the difference between the treatment received by youth with access to the Next4You platform and the treatment received by youth who instead received access to digital resources focusing on nutrition, sleep, stress and anxiety, and exercise. After the initial 4-week intervention phase, comparison group participants will retain access to the comparison website. Upon completion of the 9-month evaluation period, these participants will additionally receive access to the Next4You intervention website for the remainder of the study, concluding on September 29, 2026.

### Sample Size and Power Analyses

Our proposed sample of 500 young people (with a 1:1 allocation to each condition) would result in the Next4You evaluation being powered to identify effects in the range of small to “substantively important” (ie, 0.25 SDs, in accordance with the WWC standards) [36]. The power analysis estimates were obtained and validated via Optimal Design Plus Empirical Evidence software and the HHS Office of Adolescent Health’s Teen Pregnancy Prevention MDI and MDES calculator. The estimates were developed based on the following parameters in accordance with the funder evaluation standards: simple randomization at the individual level; 25% attrition rate; type I error rate of 5%; type II error rate of 20% (ie, power of 0.80); 2-sided hypothesis test; 50% probability of assignment to the treatment group; outcome prevalence of 50%; 25% of the outcome variance is explained by covariates. The impact model will include the baseline measure of the outcome and age or grade level, sex, and race and ethnicity as covariates consistent with funder requirements. The study team will use a combination of data- and theory-driven approaches to select additional covariates for inclusion in the model to further improve the precision of the impact estimates.

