### Outcomes

#### Primary Outcome

The primary outcome of this study is the impact of the 4-week Next4You intervention on contraceptive use among youth in foster care. Specifically, this study will examine the prevalence of participants who report either abstaining from sex or using c condoms during vaginal or anal sex in the past 3 months, compared with participants provided access to a mobile-responsive website containing only general wellness resources (sleep, nutrition, stress and anxiety, and exercise). This outcome will be assessed using data from the 3-month postintervention follow-up survey.

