#### Handling Missing Data

Missing data for all youth who agree to participate in data collection will be addressed with regression imputation using Stata, with special attention paid to WWC recommendations (eg, separately imputing data from treatment and control conditions). Regression imputation is the preferred approach for this study as it can be used to include participants with missing baseline data and missing outcome data (whereas nonresponse weighting, another imputation method, can only be used for the former). The team will use imputation regression models that (1) are conducted separately by condition or include an indicator variable for condition, (2) include all covariates used for adjustment in the impact model, and (3) include the outcome when imputing missing baseline data.

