#### Descriptive and Impact Analyses

The study team will use simple averages and frequency distributions to describe the prevalence of each outcome for youth overall and for the treatment group, by selected demographic characteristics and by usage estimates, to provide an initial understanding of changes in the primary and secondary outcomes before estimating impact estimates using multivariate models. The impact of Next4You will be estimated under the ITT framework by comparing outcomes for individuals assigned to Next4You and those assigned to the control condition. The sample will include all youth who participated in the baseline survey and completed the 3-month follow-up, 9-month follow-up, or both. The study team will model all outcomes with a linear-based 2-level multilevel regression model with youth (level 1) nested within level 2 (sites) to account for the nested structure of the data, adjust for correlated error terms, and avoid underestimating standard errors and increasing the probability of type I errors. The following 2-level random intercept multilevel model will estimate the impacts of Next4You on the primary outcome with separate models estimated for the 3- and 9-month follow-ups:

$$y_{ij}=\;\beta_{o}+\beta_{1}Treat_{1ij}+\beta_{2}Baseline_{2ij}+\beta_{3}X_{3ij}\ldots +\beta_{p}X_{pij}+u_{j}+e_{ij}$$

where $y_{ij}$ refers to the expected probability of exhibiting the corresponding outcome for individual *i* in site *j*; $\beta_{0}$ is the overall mean of the outcome across all groups; $\beta_{1}{Treat}_{1ij}$ is an indicator equal to one for participants assigned to the treatment group and zero for those assigned to the control group; $\beta_{2}{Baseline}_{2ij}$ is the baseline measure of the outcome; $\beta_{3}X_{3ij}+\ldots +\beta_{p}X_{pij}$ represents a vector of individual-level baseline covariates (such as sex, race and ethnicity, and age); $\mu_{j}$ is a site-level random effect; and $\varepsilon_{ij}$ is an individual-level error term. The estimation of the effects of the primary outcome and other dichotomous outcomes via multilevel linear probability models provides a convenient, alternative approach to logit models for interpreting dichotomous outcomes [59]. In particular, linear probability models provide model results on a probability scale that is easier to interpret, whereas logit-based versions of the models express the findings in terms of log odds that are more challenging to interpret.

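### Minor, nearly free improvement: pre-specify the baseline term of the primary model as three states (no sex, sex with condoms, sex without condoms) instead of the yes/no composite

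*Protocol article*

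**What the plan says.** The Primary Outcome section defines success as the prevalence of "participants who report either abstaining from sex or using c condoms during vaginal or anal sex" over the past 3 months. Sample Size and Power Analyses lists the covariates: "The impact model will include the baseline measure of the outcome and age or grade level, sex, and race and ethnicity as covariates". The equation under Descriptive and Impact Analyses has a single coefficient for that term, which it says "is the baseline measure of the outcome".

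Three other statements bear on the point:
- The sentence after the covariate list says that additional covariates will be selected, on data-driven and theoretical grounds, to improve precision. None is named.
- Baseline Equivalence says that baseline measures of all outcomes will enter the impact analyses. It is not clear whether each model takes its own baseline measure or all of them.
- Handling Missing Data requires that the imputation models "include all covariates used for adjustment in the impact model".

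The Study Design Overview has the study survey given at baseline, 3 months and 9 months. The article does not state how the baseline term is coded. It gives no baseline distribution of sexual activity and no follow-up rates by baseline state.

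**The concern.** A baseline yes on the composite covers two different kinds of participant: a youth who had no sex, and a sexually active youth who used condoms. Failure at follow-up means sex without a condom. The active youth is already exposed to that event and the abstinent youth mostly is not, so equal success at 3 months would be a special case. A covariate that pools the two explains less outcome variance than one that separates them.

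At stake is some precision on the single primary test. Recruitment is reported as complete, so the choice of covariates is one of the few remaining ways to gain precision. There is a second, conditional issue. If abstinent youth drop out at different rates in the two arms, adjusting for the pooled term does not fully correct for it. The imputation rule carries the same term into the imputation models.

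**Working it through.** **Inputs from Sample Size and Power Analyses.** 500 randomised 1:1; "25% attrition rate", leaving 375; 5% type I error; "2-sided hypothesis test"; power 0.80; prevalence 50% (SD 0.5); covariate R² 0.25.

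**The plan's own figure.** MDES = (1.96 + 0.84) × √[(1 − R²)/(0.25 n)] = 2.80 × √[0.75/(0.25 × 375)] = 0.251 SD. The detectable impact is 0.5 × 0.251 = 0.125, or 12.5 points. This falls within the stated 11 to 13 points and matches the stated upper effect size of 0.25 SD. Power at 12.5 points is 79.8%.

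**Gain from splitting the baseline term.** Let w be the share positive on the composite at baseline, s the abstinent share of that group, and g the gap in follow-up success between abstinent youth and condom users. Then added R² = w × s(1 − s) × g² / 0.25. Set w = 0.5. The values of s and g are assumptions. Example with s = 0.5 and g = 0.2: 0.5 × 0.25 × 0.04 / 0.25 = 0.02, so R² goes from 0.25 to 0.27.

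| s | g | R² | Variance ratio | Detectable impact (points) | Power at 12.5 points |
|---|---|---|---|---|---|
| any | 0 | 0.250 | 1.00 | 12.5 | 79.8% |
| 0.5 | 0.1 | 0.255 | 0.99 | 12.5 | 80.1% |
| 0.25 or 0.75 | 0.2 | 0.265 | 0.98 | 12.4 | 80.6% |
| 0.5 | 0.2 | 0.270 | 0.97 | 12.4 | 80.9% |
| 0.5 | 0.3 | 0.295 | 0.94 | 12.1 | 82.2% |
| 0.25 or 0.75 | 0.4 | 0.310 | 0.92 | 12.0 | 83.0% |
| 0.5 | 0.4 | 0.330 | 0.89 | 11.8 | 84.1% |

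For gaps of 0.2 to 0.4 the saving equals about 10 to 53 of the 500 randomised. A simulation of the linear probability model (n = 375, 6,000 runs, s = 0.5) gave variance ratios of 1.00, 0.97, 0.94 and 0.90 at gaps of 0, 0.2, 0.3 and 0.4, in line with the formula.

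**Second parameterisation, baseline state alone.** Assume baseline shares of 40/20/40% (no sex, condoms, condomless).
- Success 0.80/0.55/0.25: R² goes from 0.210 to 0.243 and the detectable impact from 12.8 to 12.6 points.
- Success 0.85/0.45/0.25: R² goes from 0.210 to 0.295 and the detectable impact from 12.8 to 12.1 points.

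**Differential attrition, no true effect.** Use the same shares and suppose that only abstinent Next4You youth respond less (65%), with 75% everywhere else. Among responders in the pooled group, the abstinent share is 0.26/0.41 = 0.634 in the Next4You arm and 0.30/0.45 = 0.667 in the comparison arm, a difference of −0.0325. With a gap of 0.25 (0.80 versus 0.55) this is −0.0081 within that stratum. The stratum's regression weight is 0.589, so the bias is −0.5 points. With a gap of 0.40 (0.85 versus 0.45) it is −0.8 points. If response in the other two Next4You groups is also raised to 80–85%, the range becomes −0.7 to −1.5 points. The three-state term removes the bias in all of these settings, but by construction, because dropout was made to depend only on arm and baseline state.

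**Would other baseline measures do the same job?** Taking condom use to mean no condomless sex, baseline condomless sex (the second secondary question in Textbox 1) is zero in both pooled groups, so it cannot separate them. Condom errors or attitudes could be partial proxies at most.

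**The case against.** The strongest reply is that the plan does not lock in the pooled term alone. It provides for additional precision covariates, its covariate vector is open-ended, and baseline sexual activity is an obvious candidate. Adding it to the composite would give exactly the three states. This stands: a reader might infer that the plan discards the information, but the text supports only that it does not commit to using it.

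It can also be said that covariate coding belongs in an analysis plan or in the measures appendix, neither of which is shown, and that adjusting for the baseline of the outcome is valid and follows funder requirements. That is so, and nothing here is an error. The point remains as an improvement on the one behavioural term that the article does name.

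The gain also rests on assumed rates and is negligible for gaps below about 0.1. This stands. So does the objection to a bias argument: no text in the article points to arm-dependent dropout of abstinent youth.

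Finally, the value of the split depends on the population. Textbox 1 puts the primary question among participants who had vaginal or anal sex in the past 3 months, while the Primary Outcome section has no such restriction. If analysis were limited by sexual activity at follow-up, the baseline split would still be usable but its value would change.

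**Conclusion.** A minor efficiency and pre-specification point. The only baseline behaviour term committed to for the primary model pools abstinent youth with condom users, and a three-state version from items already needed to score the composite would do at least as well, apart from one degree of freedom. For assumed gaps of 0.2 to 0.4 the benefit is about 2% to 11% lower variance and about 1 to 4 points of power; with no gap there is none.

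Two stronger readings are not supported. One is that the power statement is wrong: the 25% explained variance is assumed for the whole covariate set, and the stated detectable impact follows from it. The other is that the planned analysis is biased. Protection against attrition bias is a conditional extra, worth about 0.5 to 0.8 points if only abstinent Next4You youth drop out more (35% versus 25%), and up to about 1.5 points only if response in the other Next4You groups is also assumed to be higher.

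**What to change.** 1. Reconcile Textbox 1 with the Primary Outcome section on whether the primary analysis is restricted to sexually active participants.
2. For the primary measure at 3 and 9 months, replace the single baseline term by two indicators, sex with condoms and sex without condoms, with no sex in the past 3 months as the reference.
3. State that the same two indicators enter the imputation models under the second rule in Handling Missing Data.
4. Record this before arm codes are joined to outcome data.

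The cost is a line of analysis-plan wording and one extra coefficient among about 375 completers, with no new data.
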